## Post-Focal Therapy Treatment Efficacy/Surveillance mpMRI and MRI-TB

At 12-months from the time of FT, a SOC mpMRI and MRI-TB will be performed to determine treatment response. Both the imaging study and prostate biopsy results will be used to measure efficacy of the proposed combination treatment. However, if a patient has any other post-treatment biopsy results these may also be used to assess for post-treatment efficacy even if not performed with an mpMRI guided biopsy.

Specifically, an MRI-TB will sample the ablated and unablated prostate tissue to determine if residual CSPCa (GG ≥2) remains in the treated and/or untreated prostate tissue. The mpMRI used for the MRI-TB will follow the same imaging protocol as the pre-treatment study and reported in the same manner. Documentation of the biopsy site(s) will be required. If a new suspicious radiographic lesion(s) is/are detected on the subject’s 12-month mpMRI which was/were not present in the pre-treatment [screening] mpMRI then the targeted biopsy cores of the suspicious area(s) will be obtained. Otherwise, if no suspicious lesions are noted in the 12-month mpMRI then random biopsies from the unablated prostate tissue will be obtained per SOC during the MRI-TB.

- Two 18-gauge biopsy cores will be collected from the ablated area(s) and one each from periablation zone and untreated prostate for biobanking and exploratory outcomes on correlatives.

If the 12-month MRI-TB identifies the presence of CSPCa in the ablated or unablated prostate tissue then the patient will be offered a second treatment with FT (if eligible for such treatments) and the follow-up visits for the re-treatment will be the same as the primary treatment. The patients will stay in the study and will continue to be followed up until 12-months from the first FT procedure. For patients with residual/recurrent cancer who decline or are ineligible for a second FT procedure, one of the whole gland treatments, either radical prostatectomy, whole gland ablation or radiation therapy, will be offered. These data will be recorded as part of report of secondary outcomes. Patients who choose to undergo whole gland treatment during the study follow-up will exit the study at this point. HRQOL surveys, PSA and testosterone levels will be obtained at the exit.

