# STATISTICAL CONSIDERATIONS

## Study Design/Endpoints

This study will be a multi-institutional single arm phase I/II trial with a recruitment goal of 57 patients with treatment naïve non-metastatic intermediate-risk PCa.

Primary endpoints

1. To determine the proportion of men with CSPCa (GG ≥2) in the ablated prostate tissue by performing a surveillance mpMRI and MRI-TB at 12-months following FT.
2. To determine the proportion of men with CSPCa (GG ≥2) in the unablated prostate tissue by performing a surveillance mpMRI and MRI-TB at 12-months following FT.
3. To demonstrate the safety of combining ADT, and FT for the treatment of men with histopathologic diagnosis of GG 2 & 3 PCa, with PSA level < 20 ng/mL utilizing the NCI’s CTCAE v.5 classification to quantify and characterize the incidence of AEs.

Secondary endpoints

1. To define change in genitourinary and sexual function from baseline following ADT, and FT by measuring the subject’s HRQoL (I-PSS, SHIM, EPIC-26) at 6-and 12-months after FT.
2. To determine the PSA response to the combination treatment by measuring the subject’s PSA at “baseline” (PSA at time of initial diagnosis) and then at 3-months, 6-months, and 1-year from FT.
3. To determine the proportion of men converting to whole gland therapy (radical prostatectomy or radiation therapy) and/or requiring systemic therapy and/or developing metastases and/or dying of PCa during the course of study.
4. To determine the proportion of men without any PCa on any post treatment prostate biopsy.
5. To determine the proportion of men with normal baseline serum testosterone who had testosterone recovery (defined as testosterone levels >300 ng/dL) at 6-, 9- and 12-months after FT.

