## Sample Size/Accrual Rate

It is estimated that the 30% of men who undergo FT for intermediate-risk PCa will have CSPCa (GG ≥2) on repeat biopsy after FT. We hypothesize the combination of ADT, and FT will halve the proportion of men with residual or recurrent CSPCa to 15%. Using sample size estimates for a single proportion, comparing a null proportion of 0.30 to an alternative proportion of 0.15, with an alpha = 0.05 and power at least 80%, the total number of patients required will be 51 men. We estimate 10% attrition for a total sample size of 57 men. We are expecting 18-21 months to enroll all the patients and 36-months to complete the study.

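### The 12-month biopsy section contradicts itself on whether ablated tissue is sampled for diagnosis, so the first primary endpoint may lack a diagnostic read in MRI-clear men

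*Protocol*

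**What the plan says.** Under Study Design/Endpoints, ablated and unablated tissue are separate primary endpoints. The first reads: "To determine the proportion of men with CSPCa (GG ≥2) in the ablated prostate tissue by performing a surveillance mpMRI and MRI-TB at 12-months".

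The protocol section Post-Focal Therapy Treatment Efficacy/Surveillance mpMRI and MRI-TB (8.5 in the table of contents) makes four statements about where cores come from:

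- An opening sentence, with no MRI condition, has the biopsy sample both ablated and unablated tissue for residual Grade Group 2 or higher.
- For a new suspicious lesion, one "which was/were not present in the pre-treatment [screening] mpMRI then the targeted biopsy cores of the suspicious area(s) will be obtained".
- For a clear MRI: "Otherwise, if no suspicious lesions are noted in the 12-month mpMRI then random biopsies from the unablated prostate tissue will be obtained per SOC".
- In a separate bullet: "Two 18-gauge biopsy cores will be collected from the ablated area(s) and one each from periablation zone and untreated prostate for biobanking" and exploratory correlatives.

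Appendix B, on biopsy technique, asks for targeted cores of every lesion visible on MRI, new or not, together with systematic cores. The Missing Data paragraph imputes missing post-ablation biopsy information as positive and draws no distinction between zones.

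**The concern.** The opening sentence and the clear-MRI sentence give different instructions for the same man. Under the first he has ablated tissue sampled for diagnosis. Under the second his diagnostic cores come from unablated tissue, and his only ablated-area cores are those assigned to the bank. No passage says that the banked cores are read for Grade Group. The Biomarker Plan lists them as banking for future study and marks them O in its M/O column, which suggests that they are optional.

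The targeting sentence is also narrower than Appendix B. It mentions only lesions absent at screening, whereas Appendix B covers any visible lesion. A lesion that was treated and is still visible at 12 months is the obvious form of in-field failure, and a site reading 8.5 alone finds no instruction for it.

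Tissue that is not examined cannot yield a positive. If such a man stays in the denominator as non-positive, the observed proportion falls, and a lower proportion is what the trial counts as success. A later analysis plan can settle how he is scored, but it cannot recover cores that were never taken or never read.

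**Working it through.** **1. The passages side by side, for ablated tissue in each type of man**

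| 12-month MRI | Opening sentence of 8.5 | Specific sentence of 8.5 | Appendix B |
|---|---|---|---|
| New lesion | Sampled | Lesion targeted, wherever it lies | Lesion targeted, plus systematic cores |
| Persistent lesion only | Sampled | Silent | Lesion targeted, plus systematic cores |
| Clear | Sampled | Random cores, unablated tissue only | Systematic cores |

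The clear-MRI row contains the contradiction, and the persistent-lesion row contains a gap that Appendix B fills. Even in the first row, a new lesion need not lie in the ablated zone, so the targeted cores do not guarantee an ablated-zone read.

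**2. The plan's own sample size**

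Inputs, from Sample Size/Accrual Rate: "comparing a null proportion of 0.30 to an alternative proportion of 0.15", "with an alpha = 0.05 and power at least 80" per cent, and "the total number of patients required will be 51 men".

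n = [(z_α√(p0q0) + z_β√(p1q1)) / (p0 − p1)]²

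- One-sided 0.05: [(1.645 × √0.21 + 0.842 × √0.1275) / 0.15]² = 49.4, so 50, close to the stated 51.
- Two-sided 0.05: 63.9, so 64.
- Attrition: 51 / 0.90 = 56.7, so 57, as stated.

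The stated size is thus consistent with a one-sided 5% test.

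**3. Illustration of the bias**

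The documents give neither of the two quantities needed, so both are assumptions: f, the share of positive men whose significant cancer lies only in the ablated zone, and m, the share of those men who are missed and scored non-positive. With the true rate at the null value,

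observed rate = 0.30 × (1 − f × m)

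- f = 0.5, m = 0.2: 0.30 × 0.90 = 0.27
- f = 0.5, m = 0.4: 0.30 × 0.80 = 0.24

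The protocol states no decision rule, so three possible rules are shown. The first and third are one-sided exact 5% tests. The second requires the upper exact 95% limit to lie below 30%. The entries are exact binomial probabilities of declaring success.

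| Rule | Observed 30% | 27% | 24% |
|---|---|---|---|
| n = 57, at most 11 positive | 4.9% | 12.1% | 25.4% |
| n = 57, at most 10 positive | 2.4% | 6.8% | 16.2% |
| n = 51, at most 9 positive | 3.4% | 8.5% | 18.6% |

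The result is sensitive to f and m. With n = 57 and at most 11 positives, f = m = 0.25 gives an observed 28.1% and 8.8% false success, and f = m = 0.5 gives 22.5% and 35%. At the extreme, f = 0.5 and m = 1 give 0.30 × 0.50 = 0.15, which is the design alternative, and 86%.

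**The case against.** A reader might infer something stronger: that ablated tissue is sampled only when a new lesion appears, and that in-field disease is otherwise scored negative. The documents do not support this.

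- The opening sentence of 8.5 requires ablated tissue to be sampled without any MRI condition, and nothing ranks the later sentence above it.
- The inclusion criteria define the MRI-targeted biopsy, for this study, as systematic 12-core plus targeted. That definition sits under eligibility, but the 12-month procedure uses the same term.
- Appendix B covers any visible lesion, so persistent lesions are not left without a rule in the protocol as a whole.
- The retreatment provisions in 8.5 and in the ablation-template principles presuppose results from ablated tissue.
- No passage scores an unsampled ablated zone as negative. If the man counts as missing, he is imputed positive.

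All of this stands, and it reduces the point from a proven bias to an unresolved contradiction. It does not remove the contradiction: a site can follow the clear-MRI sentence to the letter and obtain no diagnostic ablated-zone core.

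The illustration has limits too. The 30% null refers to significant cancer on repeat biopsy without naming a zone, so it is not a null for ablated tissue. The cut-offs are not in the protocol, which plans a proportion with a 95% confidence interval. The calculation also takes every man as biopsied. If the planned attrition of 57 − 51 = 6 men were all imputed positive, the 11-positive rule would allow only 11 − 6 = 5 positives among 51. At observed rates of 27% and 24% that has probability 0.2% and 0.9%. This is a bound, because some of those men may never enter the analysis set, which requires treatment with both components.

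**Conclusion.** The point holds as an internal contradiction affecting the first primary endpoint. Section 8.5 gives two incompatible instructions for ablated tissue in MRI-clear men, assigns the ablated-area cores to banking, and words its targeting rule more narrowly than Appendix B. The missing-data rule leaves open whether a man with unablated cores only is missing for this endpoint.

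The direction is clear on one condition: if such men are not treated as missing, any loss of ablated-zone reads lowers the observed rate. The size cannot be derived from the documents. The rise from 4.9% to 12%–25% shows that modest losses could matter against a 30% null. It rests on an assumed in-field-only share of one half, an assumed miss rate of 20% to 40%, an assumed decision rule and complete biopsy data. It should not be cited as an estimate, nor should the text be said to score in-field disease as negative.

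**What to change.** Amend 8.5 and the Missing Data paragraph:

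1. Reconcile the sentences of 8.5 so that ablated-zone tissue contributes a diagnostic result in every man, whatever the 12-month MRI shows.
2. Align the targeting sentence with Appendix B, so that it covers any lesion visible on MRI and not only new ones.
3. Have the ablated-area and periablation cores already collected at this biopsy read for Grade Group before banking, and count the ablated-area reads in the first primary endpoint. Adjust the biobanking label and the O entry in the Biomarker Plan to match.
4. State that a man without an ablated-zone read is missing for the first primary endpoint, so that the existing imputation as positive applies to him.

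The biopsy session and the cores are already planned, so this is a wording amendment plus pathology reading. The costs are that some tissue meant for the bank is used first for diagnosis, and that the observed rate may be slightly less favourable. The amendment should be made before 12-month biopsies are taken, because sampling cannot be repaired at analysis.

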## For Cause Tests

Clinicians can biopsy the prostate following primary FT if there is a clinically significant rise in PSA (≥2 ng/mL higher from the subject’s post-FT PSA nadir, i.e., ‘for cause’ prostate biopsy) or clinical suspicion for progression of PCa. Nadir value will be defined as the lowest PSA value obtained after completion of combination treatment and recovery to non-castrate levels of testosterone (defined as testosterone levels >50 ng/mL). If there is a concern of prostate inflammation/infection due to a recent biopsy or urinary tract infection, patients will be treated with a course of antibiotics before repeating PSA. If the confirmatory PSA again demonstrates rise of 2 ng/mL above nadir, the patient will be evaluated further for local disease recurrence/progression. A mpMRI will be required prior to the biopsy unless the patient has developed a contraindication to biopsy.

If the untreated area is biopsied, the specimens will be individually identified according to location as determined by a standard protocol.

The specimen will be processed according to standard protocol and examined by a pathologist to note the following features for each core taken.

- Presence of adenocarcinoma
- Grade group
- Length of cancer and total core length

Additional Tests: ‘for cause’ additional tests such as ultrasound, CTAP, BS or PSMA/PET scan will be permissible as SOC practice.

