## Analysis of Primary and Secondary Endpoints

Analysis Populations

Intent-to-Treat (ITT) Population

The ITT population includes all subjects who were enrolled and treated with the combination treatment (ADT (any duration) + FT). Note: Subjects who are enrolled but not treated will be documented as screen failures. The ITT population will serve as the primary analysis set for all safety and efficacy endpoints.

Per Protocol (PP) Population

The PP population includes all subjects who were enrolled and treated with the combination treatment (ADT (any duration) + FT), and who had no major protocol deviations. The PP population will serve as a supportive analysis set for all efficacy endpoints.

Missing Data

The following imputation methods will be used for the primary analysis of all endpoints:

• When calculating the proportion of subjects with a negative biopsy for CSPCa, subjects with missing biopsy information post-ablation will be imputed as “positive”

• Missing PSA data will be imputed using last observation carried forward (LOCF) (or previous median/mean or regression-based methods if proper).

• Missing data for IIEF-5, IPSS and EPIC questionnaires will be imputed using a multiple imputation approach at the item/question level.

All other endpoints/data (e.g., safety events) will be analyzed based on available (non-imputed) data, unless specified otherwise.

Baseline demographic and clinical information will be summarized using standard summary statistics, graphs and charts (see below).

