**Descriptive tables as shown below will be populated:**

| **Baseline characteristics** |
| --- |
| Age (years), mean (SD, range) |
| Serum PSA (ng/ml), mean (SD, range) |
| Race |
| Reason for PSA test and Biopsy, % (n)  PSA screening (patient request)  Lower urinary tract symptoms |
| Prostate Volume (mL), mean (SD, range) |
| PSA Density (ng/mL^2^), mean (SD, range) |
| Grade group score on MRI-TB, % (N)  3+4  4+3 |
| MRI-TB, mean (SD, range)  Total Cores  Total Positive Cores  % Positive Cores |
| Risk category (%, n)  Unfavorable intermediate-risk |

| **Peri-operative characteristics** |
| --- |
| Procedure time (minutes), mean (SD, range) |
| Procedure type: HIFU or Cryoablation |
| Discharge time from procedure end (hours), mean (SD, range) |
| Length of catheterization (days), mean (SD, range) # |
| Dysuria (negative urine culture), % (n)  Duration (days), mean (SD, range) |
| Intermittent hematuria (start of stream only), % (n)  Duration (days), mean (SD, range) |
| Urinary debris, % (n)  Duration (days), mean (SD, range) |
| Urinary tract infection (positive urine culture) (%, n) |
| Stricture (%, n) |
| Recto-urethral fistula (%, n) |

| **Histological characteristics at 12-months MRI-TB** |
| --- |
| Number of cores taken, mean (SD, range) |
| PSA density (ng/mL^2^), mean (SD, range) |
| Absence of any cancer (%, n) |
| Absence of Gleason pattern 4 (%, n) |

The primary objective will be expressed as proportions of total number of patients and the 95% confidence interval of the proportion will be presented. Number and grade of complications will be reported.

HrQOL measures collected at 6- and 12-months will be compared to baseline measures using paired tests. In addition, the 6-month and 12-month change from baseline will also be tabulated

PSA: The mean PSA levels at each visit, the overall percent reduction in PSA levels from baseline to each visit, and the proportion of subjects with a PSA reduction compared to baseline at each visit will be presented. Mean PSA nadir and post-nadir PSA values through 12-months post-treatment will be summarized.

Testosterone recovery: Number of men who have recovered normal serum testosterone levels will be expressed as proportions of total number of eugonadal patients and the 95% confidence interval of the proportion will be presented.

Secondary or Adjuvant Treatment: The number and proportion of subjects undergoing secondary treatment during the study will be presented.

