**Calendar Footnotes**

1. ADT therapy will consist of any generic luteinizing hormone-releasing hormone agonist which will provide 3-months of treatment (e.g.,.
2. Focal therapy to be completed within 8- to 12-weeks of the initiation of ADT but after the completion of the 8-week mpMRI to allow for it to be used in FT planning.
3. Both adverse events (AEs) and serious AEs and any conmeds to be collected from the time of consent and continuously throughout the study until 30-days after the FT or as indicated in Section 14 of this protocol.
4. Focused abdominal and pelvic genitourinary exam. To be completed once a subject has entered into post-FT follow-up and only as clinically indicated.
5. Vital signs should include: temperature, pulse, respiratory rate, height, weight and blood pressure.
6. Health related quality of life measures including EPIC-26, the I-PSS and the SHIM must be collected at screening. If any of these are not done at screening then these may be completed at Visit 2.
7. PSA collected at “baseline” is defined within eligibility for this protocol. PSA and testosterone value is collected at 3-, 6-, 9- and 12-months post-FT.
8. Screening CBC & CMP, and testosterone must be collected and reviewed for safety within 15-days prior to the initial dose of ADT. Collection at other timepoints only if clinically indicated.
9. A single purple top EDTA tube of 3mL of whole blood to be collected after eligibility is confirmed for banking for future germline testing and at 6-weeks after FT. At the time of FT two 18-gauge biopsy cores will be collected from the target area(s) and one each from peritumoral and untreated prostate. At the time of 6-month MRI-TB two 18-gauge biopsy cores will be collected from the ablated area(s) and one each from periablation zone and untreated prostate.
10. Long term follow-up (LTFU) data collection to begin at 6-weeks after FT and includes collection of any recurrence, re-treatment, survival, and other relevant post-surgical data through 1-year post-FT.
11. FT foley catheter to be removed 1 weeks after FT +/- 3 days.

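### The PSA nadir rule sets non-castrate testosterone at >50 ng/mL (5,000 ng/dL), 16.7 times the protocol's own level for full recovery; the unit is almost certainly wrong

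*Protocol*

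**What the plan says.** The Protocol's section For Cause Tests gives two routes to a biopsy outside the schedule. The PSA route begins "Clinicians can biopsy the prostate following primary FT if there is a clinically significant rise in PSA", where the rise must be at least 2 ng/mL over the post-FT nadir. The other route is the clinician's suspicion that the cancer is progressing.

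The nadir is the smallest PSA measured once two conditions are met: the combined treatment is over, and there has been "recovery to non-castrate levels of testosterone (defined as testosterone levels >50 ng/mL". Where inflammation or infection is a concern, PSA is repeated after antibiotics, and the repeat is judged against the same nadir: "If the confirmatory PSA again demonstrates rise of 2 ng/mL above nadir, the patient will be evaluated further for local disease recurrence/progression".

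The only other testosterone threshold is in Study Design/Endpoints. Secondary endpoint 5 counts men with "testosterone recovery (defined as testosterone levels >300 ng/dL", assessed at 6, 9 and 12 months after FT.

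Testosterone is drawn alongside PSA. The Calendar Footnotes state that "PSA and testosterone value is collected at 3-, 6-, 9- and 12-months post-FT".

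**The concern.** Non-castrate should be the lower hurdle and recovery to a normal level the higher one. As printed, the order is reversed by more than a factor of ten.

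The figure does work in the protocol. It decides which PSA values may serve as the nadir, and both the 2 ng/mL trigger and the confirmatory PSA are measured from that nadir. If no PSA qualifies, neither step can be carried out as written.

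Two later uses give the rule some weight beyond the clinic visit:

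- The section on post-FT surveillance lets results of other post-treatment biopsies count toward efficacy.
- The ablation-template principles allow one repeat FT after a positive for-cause biopsy.

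**Working it through.** The threshold is a definition, so there is no planned figure to reproduce. The check converts both testosterone thresholds to one unit and follows the consequence through the rule.

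**Inputs**

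- Non-castrate threshold: >50 ng/mL (For Cause Tests).
- Recovery threshold: >300 ng/dL (Study Design/Endpoints, secondary endpoint 5).
- Conversion: 1 dL = 100 mL, so 1 ng/mL = 100 ng/dL.

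**Step 1: common unit**

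- Non-castrate: 50 ng/mL × 100 mL/dL = 5,000 ng/dL.
- Recovery: 300 ng/dL ÷ 100 = 3 ng/mL.

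**Step 2: comparison**

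- 5,000 ÷ 300 = 16.7. The non-castrate level is 16.7 times the recovery level.

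**Step 3: the presumed intended unit**

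- 50 ng/dL ÷ 100 = 0.5 ng/mL, which is below 3 ng/mL. A man would pass the non-castrate level first and the recovery level later, so the two definitions would be coherent.
- The printed value is 5,000 ÷ 50 = 100 times this one. That ratio compares with an inferred value; the 16.7 compares two figures that both stand in the protocol.

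**Step 4: effect on the nadir**

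A site faced with the conflict could apply the printed value, assume ng/dL, or borrow the 300 ng/dL level. The table shows whether the testosterone condition for a nadir is met under each.

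| Testosterone | As printed (>5,000 ng/dL) | Unit read as ng/dL (>50) | Recovery level borrowed (>300) |
| --- | --- | --- | --- |
| up to 50 ng/dL | no | no | no |
| above 50, up to 300 | no | yes | no |
| above 300, up to 5,000 | no | yes | yes |
| above 5,000 | yes | yes | yes |

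The third row holds the contradiction: such a man is recovered for the secondary endpoint, yet not non-castrate for the nadir. With no nadir, a rise of 2 ng/mL above it is undefined, both at the first PSA and at the confirmatory one. The second row shows that the two plausible repairs also differ, so they could qualify different PSA values as the nadir in the same man.

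**The case against.** The strongest reply is that this is a slip in one unit that any urologist would see through. The sentence itself speaks of non-castrate levels, and the endpoint section gives testosterone in ng/dL. Nor is any mandatory protection switched off. The biopsy is something clinicians may do, not something they must do. Clinical suspicion stands as an independent route, and nothing stops a clinician from treating a PSA rise as grounds for it. Additional imaging is allowed as standard practice. Finally, "At 12-months from the time of FT, a SOC mpMRI and MRI-TB will be performed to determine treatment response", whatever the nadir.

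Most of this stands, and it limits the point to a minor one. It does not remove the point. The trial is multi-institutional, monitoring checks adherence to the protocol, and only the Study Lead PI may change its text. A site that quietly applies another value is departing from what is written, and the table above shows that sites could depart in different ways.

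A reader might infer three stronger things that the documents do not support:

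- **That for-cause work-up is disabled.** Only the PSA route is affected, and only on a literal reading that sites would probably not adopt.
- **That the planned summary of PSA nadir cannot be produced.** The analysis section plans that "Mean PSA nadir and post-nadir PSA values through 12-months post-treatment will be summarized", but it does not say that it uses the For Cause Tests definition. How a descriptive nadir is derived can properly be left to the SAP, which is not at hand.
- **That the main result or the sample size is undermined.** Neither the primary endpoint's definition nor the calculation leading to 51 and then 57 men uses this threshold.

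The opposite claim, that efficacy is wholly untouched, is also too flat. Other post-treatment biopsies may be used for efficacy, and secondary endpoint 4 refers to any biopsy after treatment. The documents give no basis for a size or direction of that effect.

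**Conclusion.** Wrong as written, and minor. The protocol sets the non-castrate threshold at 5,000 ng/dL against its own recovery level of 300 ng/dL, a 16.7-fold reversal that shows from the document alone. On the literal text, a man above 300 but not above 5,000 ng/dL has no PSA nadir, and the 2 ng/mL trigger and confirmatory step have nothing to be measured from.

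The contradiction rests only on the unit conversion and the two printed thresholds. That the intended value is 50 ng/dL is an inference: it fits the wording and restores the order of the two levels, but the protocol does not state it. How many men or biopsies would be affected cannot be computed from the protocol, which gives neither testosterone levels after FT nor an expected number of for-cause biopsies.

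**What to change.** In For Cause Tests, change the unit of the non-castrate testosterone threshold from ng/mL to ng/dL, and have the investigator confirm the value (probably >50 ng/dL).

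The cost is one unit in one sentence, carried in the next amendment. No patients, visits or blood draws are added, because testosterone is already measured with PSA at each scheduled visit from 3 months after FT. Endpoint definitions and sample size stay as they are.
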